### Eligibility criteria {10}

#### Inclusion criteria

The following are the inclusion criteria:Patients 18–85 years of agePatients with the signing of informed consent and confirming enrollmentACLF was diagnosed according to guidelines for diagnosis and treatment of liver failure (2018) [13]: a presentation of extreme fatigue and severe gastrointestinal symptoms (anorexia, abdominal distension, nausea, and vomiting), progressive jaundice over a short period (total serum bilirubin ≥ 10 × ULN or a daily rise ≥ 17 μmol/L), a pronounced bleeding tendency (PTA ≤ 40% or INR ≥ 1.5), and any degree of potential complications (encephalopathy, clinical ascites, etc.) based on ongoing chronic liver diseasesIPA was diagnosed according to the latest EORTC/MGC consensus definition updated in 2020 [14, 15], including proven and probable IPAProven IPA: histopathologic examination of a pulmonary specimen obtained by needle aspiration or biopsy in which hyphae or melanized yeast-like forms are seen accompanied by evidence of associated tissue damage or recovery of the aspergillus by the culture of the alveolar lavage fluid obtained by a sterile fiberoptic bronchoscope lavage from a normally sterile and clinically or radiologically abnormal site consistent with an infectious disease processProbable IPA: host factors + clinical features (fever, cough, sputum, and other symptoms; signs such as rales in the lungs; pulmonary imaging in support of aspergillus infection) + mycological evidence

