#### Dropout criteria

The following are the dropout criteria:Patients with ALT or TBiL continuous elevation (more than 5 or 2 times higher than the baseline)Patients with central nervous system toxicity such as hallucinations and psychiatric abnormalities and plasma voriconazole trough concentration persistently exceeding 6 mg/L, which cannot be relieved by reducing the dose to 50 mg qdPatients who withdraw their consent during the study

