### Criteria for discontinuing or modifying allocated interventions {11b}

Persistent high trough concentrations are an independent risk factor for hepatic and central toxicity of voriconazole. Therefore, if ALT or TBiL is persistently elevated (i.e., a fivefold increase for ALT or a twofold increase for TBil above baseline) or central nervous system toxicity such as hallucinations and psychiatric abnormalities occur, and plasma voriconazole trough concentration persistently exceeding 6 mg/L, which cannot be relieved by reducing the dose to 50 mg qd, voriconazole can be discontinued and replaced with echinocandins for antifungal treatment or even withdrawn from the trial. A patient may also be withdrawn from the study for the following reasons: (1) lost to follow-up or (2) withdrawal of consent.

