### Plans to promote participant retention and complete follow-up {18b}

The purpose and importance of the trial will be explained through the research team and PICF during participant recruitment. Participants have the right to withdraw from the trial at any time and for any reason without compromising their medical care and routine treatment by the treatment team or institution. If a participant withdraws from the trial before the end of the study and because the data will be recorded anonymously, an intention-to-treat analysis will be performed on the data for such patients. If a patient withdraws consent during the conduct of the trial and does not wish to consent to the use of data already collected, and if these particular data are retrievable, the investigator will delete the data accordingly.

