## Statistical methods

### Statistical methods for primary and secondary outcomes {20a}

In this study, a separate statistical analysis plan will be developed to analyze the data of the treatment group and the control group. The analyses will be based on Consolidated Standards of Reporting Trials guidelines, and all analyses will be on the principle of intention-to-treat, that is, all participants will be analyzed even if some subjects will fail to follow the original plan during the study. This analysis method can better evaluate the effect of the intervention, reduce bias, and be closer to the actual clinical situation. Our researchers are responsible for the follow-up to ensure that relatively complete data are obtained. Subjects who lacked data on the main results will be excluded in the study from the beginning, including missing CYP2C19 gene, lung CT, abdominal ultrasound, G/GM test, Child–Pugh score, and MELD score.

The PASW18.0 statistical software will be used to analyze the data. The counting data will be expressed by rate, and the rate will be compared by the chi-square test. Continuous normal distribution data will be expressed as mean ± standard deviation, *t*-test will be used for comparison between the two groups, non-normal data will be expressed as median (quartile spacing), Mann–Whitney test method will be used for comparison between the two groups, and *χ*^2^ test will be used for counting data. *P* < 0.05 indicates that the difference is statistically significant. The GraphPadPrism5 software will be to draw.

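### A continuous ALT or bilirubin rise is a stand-alone dropout criterion in one section but an optional stop, naturally read as also needing a high trough, in another, so ACLF progression alone can meet it

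*Protocol article*

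**What the plan says.** Two sections of the Protocol article deal with the same liver event.

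- **Dropout criteria.** Three items are listed. The first is "Patients with ALT or TBiL continuous elevation (more than 5 or 2 times higher than the baseline"), with no trough condition and no attribution to voriconazole. The second, central nervous system toxicity, carries the condition of a trough above 6 mg/L not relieved at 50 mg once daily. The third is withdrawal of consent.
- **Criteria for discontinuing or modifying allocated interventions {11b}.** The section opens with a rationale: "Persistent high trough concentrations are an independent risk factor for hepatic and central toxicity of voriconazole". One sentence then names the liver limits ("a fivefold increase for ALT or a twofold increase for TBil above baseline"), or central nervous system toxicity, and after a comma adds "plasma voriconazole trough concentration persistently exceeding 6 mg/L, which cannot be relieved by reducing the dose to 50 mg qd". The consequence is that "voriconazole can be discontinued and replaced with echinocandins for antifungal treatment or even withdrawn from the trial".

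The inclusion criteria require ACLF with progressive jaundice, specified as "total serum bilirubin ≥ 10 × ULN or a daily rise ≥ 17 μmol/L". On withdrawals, section 18b says that "an intention-to-treat analysis will be performed on the data for such patients", and section 20a that "all analyses will be on the principle of intention-to-treat". Section 20c plans no imputation.

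**The concern.** An investigator whose patient's bilirubin has doubled while the trough is in range gets two answers. Under the Dropout criteria the patient meets a criterion for leaving the trial. Under section 11b, read naturally, the patient does not qualify even for the optional stop.

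This matters in this population because rising bilirubin is part of the disease that qualifies patients for entry. A criterion with no link to drug exposure can be met by ACLF progression alone. The possible costs are avoidable stopping of the first-line antifungal, or the end of trial assessments, in patients whose liver disease is worsening. Response is judged partly on CT, and with no imputation planned, a response left unassessed would not be replaced.

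**Working it through.** **The two rules side by side**

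| | Dropout criteria | Section 11b |
|---|---|---|
| Liver limits | ALT 5 ×, TBil 2 ×, continuous | ALT fivefold, TBil twofold, persistent |
| Trough condition on the liver limb | none | yes on the natural reading; no on the alternative parse |
| Consequence | listed as dropout | may stop and switch, or even withdraw |

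Two features of section 11b favour attaching the trough condition to both limbs: the comma before the trough clause, and the opening sentence tying high troughs to hepatic as well as central toxicity. The alternative parse is liver elevation, or central toxicity with a high trough. It removes the difference in the second row but leaves the third.

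**Can disease progression alone meet the dropout criterion in 8 weeks?** The plan gives no figure to reproduce, so this is an illustration only.

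Inputs:
- b = baseline TBil. The ULN is not given; assuming 17–21 μmol/L, 10 × ULN is 170–210. A baseline of 400 is added as a higher case.
- r = rise per day: 17 μmol/L from the inclusion criterion, and half of that (8.5). Both are assumed linear and sustained. The protocol does not require the rise to continue after dosing.
- a = age in days of the baseline sample at the first dose: 0, or 7 as the extreme. Table 1 gives a window of −7 for the baseline visit; its unit is not printed and is taken as days.
- k = 2 or 3, because a value two times higher than baseline can mean 2 × or 3 × baseline.

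Days after first dose to reach k × baseline = (k − 1) × b / r − a.

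| b | r | a | to 2 × | to 3 × |
|---|---|---|---|---|
| 170 | 17 | 0 | 170/17 = 10.0 | 340/17 = 20.0 |
| 210 | 17 | 0 | 210/17 = 12.4 | 420/17 = 24.7 |
| 400 | 17 | 0 | 400/17 = 23.5 | 800/17 = 47.1 |
| 170 | 17 | 7 | 10.0 − 7 = 3.0 | 20.0 − 7 = 13.0 |
| 210 | 17 | 7 | 12.4 − 7 = 5.4 | 24.7 − 7 = 17.7 |
| 170 | 8.5 | 0 | 170/8.5 = 20.0 | 340/8.5 = 40.0 |
| 210 | 8.5 | 0 | 210/8.5 = 24.7 | 420/8.5 = 49.4 |
| 400 | 8.5 | 0 | 400/8.5 = 47.1 | 800/8.5 = 94.1 |

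**If continuous means two consecutive scheduled tests.** Table 1 puts post-baseline biochemistry at days 3, 7, 14, 21, 28, 42 and 56. The ratio to baseline at day v is (b + r(v + a))/b. With a fresh baseline:

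- r = 17, limit 2 ×, b = 170/210: day 14 gives 2.40/2.13 and day 21 gives 3.10/2.70, so met at week 3.
- r = 17, limit 2 ×, b = 400: day 28 gives 2.19 and day 42 gives 2.79, so met at week 6.
- r = 17, limit 3 ×, b = 170: day 21 gives 3.10 and day 28 gives 3.80, so met at week 4.
- r = 17, limit 3 ×, b = 210: day 28 gives 3.27 and day 42 gives 4.40, so met at week 6.
- r = 17, limit 3 ×, b = 400: only day 56 exceeds the limit (3.38), so not met.
- r = 8.5, limit 2 ×: met at week 4 (b = 170) or week 6 (b = 210). For b = 400 only day 56 exceeds the limit (2.19), so not met.

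No ALT course is given, so nothing is computed for ALT.

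**The case against.** The strongest reply is that section 11b repeats the elements of the Dropout criteria in the same order, and the latter tie the trough to central toxicity only. Read together, the trough conflict disappears. That parse is possible, though less natural. It leaves a listed dropout criterion against a permissive stop.

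It can also be said that a stand-alone liver stop is a defensible precaution for a hepatotoxic drug in liver failure, and the adverse event section counts deterioration of liver function among possible adverse events. That stands as an argument about stopping the drug, and the repair has to respect it. It does not justify leaving the trial.

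The illustration combines two inclusion limbs that are joined by *or*, so a given patient need not have both 10 × ULN and a rise of 17 μmol/L per day. It shows what can happen, not what is typical.

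A reader might infer more than the documents support:

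- **That efficacy data are lost.** Three of the four post-baseline CTs (weeks 2, 4, 6 and 8) would still be due if the rule is met at week 3. But the Dropout criteria do not say that CT or follow-up ends, intention-to-treat is stated, and the primary outcome section fixes no assessment time for response. Loss is possible, not stated.
- **That one arm is favoured.** Nothing in the documents shows this.
- **That the 10% dropout allowance is exceeded.** No frequency is given. The sample size is also built on the day-3 trough, drawn at the same 72 h visit as the first post-baseline biochemistry, so exit under this criterion would come no earlier than that measurement.

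**Conclusion.** The concern holds as a minor inconsistency. What is certain is that the same liver limits are a dropout criterion in one section and an optional ground for stopping or withdrawal in the other. What is likely, on the natural reading of section 11b, is that the two also differ on whether a high trough is needed.

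Disease progression alone can meet the stand-alone criterion within follow-up. From 170–210 μmol/L at 17 μmol/L per day with a fresh baseline, the limit is reached in about 10–12 days if it means 2 × baseline, or about 20–25 days if it means 3 ×. This rests on the assumed ULN and on a sustained linear rise. With a slower rise or a higher baseline it comes later, and in some cases not by week 8. The frequency is unknown, and an effect on the treatment comparison is not demonstrated.

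**What to change.** State one rule in both sections:

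1. Make the liver limits a trigger for a trough check, dose reduction or stopping of voriconazole, with the trough condition as in section 11b. Give the investigator explicit discretion to stop for suspected drug-induced liver injury at any trough.
2. Do not make the liver limits an automatic exit from the trial. Continue scheduled CT, response and mortality follow-up after voriconazole is stopped, in line with the intention-to-treat principle in sections 18b and 20a.
3. Write the limits as multiples of the baseline value, for example TBil > 2 × baseline.
4. Take baseline ALT and TBil from the last sample before the first dose. The −7 window can stay for CT, ultrasound, genotype and mycology.

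The cost is one reworded rule, a footnote to Table 1 and an occasional extra pre-dose blood sample in inpatients. The real downside is reliance on investigator judgement for liver injury at troughs of 6 mg/L or below. If the sponsor prefers a stand-alone liver stop on safety grounds, aligning section 11b to it would also remove the inconsistency. In that case it should stop the drug, not trial follow-up, and disease progression alone could still trigger it.

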### Who will take informed consent? {26a}

Informed consent will be obtained by the investigators.

There will be an investigator on our team who will be specifically responsible for engaging with patients to participate in the study. The investigator will be responsible for providing each patient and family member with a Participant Information and Consent Form (PICF) describing the purpose and procedures of the study, foreseeable benefits and potential risks of participation, information on data protection procedures, and the option to withdraw from the study at any time, and no reason is required, which should be read by the patient. The investigator will answer any questions the patient and family members may have, and both the patient or his or her family and the investigator will sign the informed consent form to demonstrate the patient’s and family’s full understanding of the study. Written informed consent must be obtained from all participants prior to any trial-related procedures and prior confirmation that inclusion/exclusion criteria are met during the eligibility assessment is required before patient enrollment.

### Additional consent provisions for collection and use of participant data and biological specimens {26b}

In the PICF, the participants will be informed about the use and storage of personal data and biological specimens collected during their participation in the trial. The PICF also contains information concerning the personnel who can access the data collected during this trial and the period that the data will be kept following the study’s completion. By signing the informed consent form, the participants agree to the terms addressed in the PICF.

## Interventions

### Explanation for the choice of comparators {6b}

Instruction of voriconazole shows no recommendation for patients with severe liver cirrhosis (Child–Pugh C) and liver failure, so the choice of comparators in this study is based on the recent research on related topics and the previous retrospective studies of our research group [3, 7, 10, 11, 16–18]. The recommended protocol of voriconazole for Child–Pugh A or B liver cirrhosis was chosen as a control to best determine any effects of the interventions.

### Intervention description {11a}

Eligible patients will be randomized to either the experimental group or the control group. According to the recent research on related topics and the previous retrospective studies of our research group, the experimental group will receive the optimized voriconazole regimen: first loading dose, 6 mg per kilogram intravenously; second loading dose (twelve hours interval from first dose), 2 mg per kilogram intravenously; maintenance dose, 2 mg per kilogram intravenously twice daily.

### Criteria for discontinuing or modifying allocated interventions {11b}

Persistent high trough concentrations are an independent risk factor for hepatic and central toxicity of voriconazole. Therefore, if ALT or TBiL is persistently elevated (i.e., a fivefold increase for ALT or a twofold increase for TBil above baseline) or central nervous system toxicity such as hallucinations and psychiatric abnormalities occur, and plasma voriconazole trough concentration persistently exceeding 6 mg/L, which cannot be relieved by reducing the dose to 50 mg qd, voriconazole can be discontinued and replaced with echinocandins for antifungal treatment or even withdrawn from the trial. A patient may also be withdrawn from the study for the following reasons: (1) lost to follow-up or (2) withdrawal of consent.

### Strategies to improve adherence to interventions {11c}

The following measures will be, and or have been, taken to improve adherence to interventions and follow-up:All participants will be informed of the study procedures as well as potential benefits and risks to make them fully understand the significance of their involvement in the study.All participants will receive two free voriconazole blood tests and will be able to use first-line therapeutic agents with closely monitored drug blood levels and adverse effects for better outcomes.

### Relevant concomitant care permitted or prohibited during the trial {11d}

There will be no restrictions regarding concomitant care during the trial.

### Provisions for post-trial care {30}

All patients will return to standard care after the trial.

### Outcomes {12}

#### Primary outcome

The primary endpoint will be the antifungal efficacy of voriconazole. All patients treated with voriconazole were systematically evaluated by the same investigator on the team. Each patient was evaluated on the basis of case report, imaging (computed tomography scan, CT) findings. CT images of the lung were reviewed by two radiologists. Changes in lesions were assessed visually using computed planimetry to help estimate percentage change. The response categories for complete response, partial response, and treatment failure were the same as those in similar previous studies [16–19]. Complete responses were defined by the resolution of all clinical signs and symptoms and more than 90% of the lesions due to invasive aspergillosis that were visible on radiology. Partial responses were defined by clinical improvement and greater than 50% improvement in findings on radiology. Stable responses were defined by the absence of change from base line or an improvement of less than 50%. Failure of therapy encompassed progression and death due to IPA. Complete and partial responses were classified as successful outcomes.

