## Assignment of interventions: blinding

### Who will be blinded {17a}

This study is a non-double-blind trial.

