### Procedure for unblinding if needed {17b}

The design is open label, so unblinding will not occur.

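### The primary response rests on visual CT estimates and clinical judgement in an open-label trial, and no assessor is stated to be masked; masked CT reading would reduce the bias cheaply

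*Protocol article*

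**What the plan says.** All of this is in the Protocol article. Under Outcomes {12}, Primary outcome:

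- Overall rating: "All patients treated with voriconazole were systematically evaluated by the same investigator on the team".
- CT reading: "CT images of the lung were reviewed by two radiologists", and "Changes in lesions were assessed visually using computed planimetry to help estimate percentage change".
- Partial response: "Partial responses were defined by clinical improvement and greater than 50% improvement in findings on radiology". Complete response needs all clinical signs and symptoms and more than 90% of the visible lesions to have resolved. Improvement of less than 50% counts as stable.
- Success: "Complete and partial responses were classified as successful outcomes".
- Failure: "Failure of therapy encompassed progression and death due to IPA".

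Under Who will be blinded {17a} the whole answer is "This study is a non-double-blind trial". Under Procedure for unblinding {17b} it is "The design is open label, so unblinding will not occur". Neither item, nor the outcome section, says that the radiologists or the rating investigator are kept unaware of the arm.

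**The concern.** The line that matters for the primary comparison is the 50% cut. Above it, with clinical improvement, a patient is a success; below it the patient is stable and not a success. Both components involve judgement: the percentage change is a visual estimate aided by planimetry, and clinical improvement is rated by one member of the trial team. If the person judging a borderline case knows the regimen, expectation can tip it, and can do so differently in the two arms.

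An error of that kind does not average out. It can produce a difference where there is none or hide a real one. Under the non-inferiority label in Trial design {8}, a tilt toward the experimental arm adds directly to its apparent result. A larger sample does not correct it, and neither can an analysis plan, because masking has to be in place when the scans are read and the patients rated. Open-label dosing may be unavoidable, but it does not require open-label reading of stored CT images.

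**Working it through.** **The documents.** No figure in the plan bears on this point, so the first step is to set the sections side by side. Outcomes {12} names the assessors (one investigator, two radiologists) and the judgements they make. Item {17a} is the place where masked parties would be named, and it names none. Item {17b} gives open label as the reason why no unblinding procedure is needed. Confidentiality {27} already gives each participant a subject number, so images can be identified by number alone.

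**How far a shift could matter.** Inputs from the plan: 48 per arm (Sample size {14}); rates compared by the chi-square test at P < 0.05 (Statistical methods {20a}). Assumed inputs: a true response rate p of 0.30 or 0.40, equal in both arms, because the article gives no expected response rate; and a net shift s in the rated response of one arm only, because nothing in the article says how large misrating might be.

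With x and y rated successes in the two arms and m = (x + y)/96,

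χ² = ((x − y)/48)² / (2·m·(1 − m)/48), significant if χ² > 3.841.

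The chance of a significant result is the sum, over all significant pairs (x, y), of Bin(x; 48, p + s) × Bin(y; 48, p).

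| Shift s | Patients in one arm (48 × s) | p = 0.30 | p = 0.40 |
|---|---|---|---|
| 0 | 0 | 0.052 | 0.049 |
| 5 points | 2.4 | 0.084 | 0.079 |
| 10 points | 4.8 | 0.177 | 0.168 |
| 15 points | 7.2 | 0.329 | 0.319 |

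**The reverse direction.** Suppose true response is 0.30 against 0.50. With unbiased rating the test is significant about 52% of the time. If a 10-point shift favours the worse arm, the rated rates are 0.40 and 0.50. That is the same pair as the last column at 10 points, so detection falls to about 17%.

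**Non-inferiority reading.** The article gives no margin, so this needs a further assumption. The setting is a normal approximation at 48 per arm, margins of 10 to 20 points, control response of 0.4 to 0.6, and an experimental arm truly worse by exactly the margin. Reading 10% of that arm's non-responders as responders then raises the one-sided error from 2.5% to about 7–13%.

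**The case against.** Several objections have force.

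- *The radiologists are not said to be unmasked.* Correct: this is inferred. The two items describe the trial as a whole, and a condensed article may leave reading procedures to the full protocol. But {17a} is not silent. It is answered, and the answer masks nobody, so the fair statement is that no masking is stated.
- *The plan already limits discretion.* It does, through numerical cuts, planimetry, two readers and one consistent rater. These reduce random variation. They do not protect against an expectation that the raters share.
- *The team's expectation favours the experimental arm.* A reader might infer this from Background and rationale {6a}, which judges the regimen recommended for milder cirrhosis unsuitable for these patients. The documents do not support that reading for the primary outcome. The judgement there rests on high concentrations and toxicity, not on poorer antifungal response, and nothing attributes it to the radiologists. The Discussion even worries that a lower dose may delay treatment. The direction of any bias is therefore unknown.
- *Attribution of death decides success.* A reader might infer this too. For a patient who never responded, attributing the death to IPA or not separates failure from unclassified, and neither is a success. It could matter only for a patient who responded and then died.
- *The magnitude is hypothetical.* It is. The smallest shift takes the error only from 5% to 8%, and no evidence in the article shows which shift is realistic.
- *Masking the clinical rater may not be just a matter of wording.* This stands. Table 1 puts condition evaluation at the same visits as trough sampling. If the designated investigator carries out those visits, someone else must prepare the summary.

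**Conclusion.** The point holds in a limited form. The primary response depends partly on judgement, the trial is open label, and no assessor is stated to be masked, so the result is open to expectation bias in either direction. At 48 per arm, a one-arm shift of about 5 patients (10 points) would roughly triple the false-positive rate, to 17–18%, and a shift of 2 to 3 patients would raise it to about 8%. These figures illustrate sensitivity; they do not estimate bias in this trial, since the response rates and the shifts are both assumed.

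It is tempting to say that masking the existing readers would remove the problem. The documents do not support that. Masked CT reading leaves the clinical half of the definition, whose masking may be imperfect when toxicity is obvious. It also leaves differences in open-label care: concomitant care is unrestricted under {11d}, and {11b} allows study drug to be stopped and replaced. The supportable claim is a worthwhile reduction in bias at small cost.

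**What to change.** In Outcomes {12} and Who will be blinded {17a}, state that:

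1. the same two radiologists read CTs identified by study number only, masked to arm, dose and trough concentration;
2. they resolve disagreements by consensus while still masked;
3. the agreed percentage change is recorded and locked before any clinical data are seen, and the radiological component of response is derived from that locked value;
4. where feasible with existing staff, the designated investigator rates the clinical component from a summary that omits arm, dose and trough.

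State also that dosing remains open label and that masking of the clinical component may be incomplete.

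Items 1 to 3 cost protocol wording and de-identification of images, with the same readers and no extra scans. Stored CTs of patients already enrolled can still be read this way. Item 4 also takes some staff time to prepare summaries, which is why it is conditional.
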